## Methods

### Design

This is a double-blinded randomized placebo-controlled phase II trial of anakinra in patients diagnosed as having dengue with warning signs/severe dengue and hyperferritinaemia (>2000 ng/ml) (
Figure 1). The study will enrol 160 adults and children ≥ 12 years old admitted to the Hospital for Tropical Diseases, Ho Chi Minh City. Participants will be randomized 1:1 (anakinra:placebo) on electronic database system (Ennov) and stratified according to the ward of recruitment (Intensive Care Units/Emergency Department or the general dengue wards). Patients with warning signs or severe dengue (defined by 2009 WHO classification) and ferritin > 2000 ng/ml will be eligible for enrolment.

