### Primary endpoint

The primary endpoint of this study is the delta mSOFA score* (change in mSOFA score over 4 days after randomization).

*mSOFA = modified Sequential Organ Failure Assessment score (modified for resource limited settings and dengue) see Appendix 1 for score.

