### Randomization

After confirmation of eligibility, including obtaining ICF for randomization phase, study doctors will perform randomization on the electronic data system (Ennov). Randomization will be minimization at 1:1 ratio and stratified according to the ward of recruitment. The system will assign a unique study ID and drug code for the patient. The assigned drug code will correspond to a sealed pre-packaged box containing 08 doses (bd dosing for 4 days) of either anakinra or visually matched placebo for adults or children. Drug appearance and administration schedules will be identical to maintain blinding amongst the attending physicians and nurses. Neither the patients nor the study assessors, including treating physicians, study doctors/nurses, know which group patients in.

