### Statistical considerations

**
*Sample size.*
** Given that delta mSOFA score has an approximately normal distribution
^
25
^ with a standard deviation of 2.4, which was based on a cohort of 38 adults admitted with severe dengue, we would need a sample size of 80 patients per group to detect a between-group difference of at least 1.0 point with 80% power and 5% type-I error rate.

**
*Statistical analysis.*
** The primary endpoint (delta mSOFA score) and the secondary endpoints (ALT, CRP, PLTs and ferritin) will be analyzed using a linear mixed-effects model, which models their values over the first 4 days for mSOFA and 5 days for lab tests (as specified in sections 2.4.1 and 2.4.2). We will use a linear trend for time as fixed and random effects. The slope of this model reflects the change in value over time. Therefore, the effect of anakinra is measured as the difference in slope between treatment groups. This difference will be assessed via the interaction between time and treatment group in that model, and presented with a corresponding 95% confidence interval. For the change at day 30 (ferritin and CRP) we will use the difference with the value at randomisation. Mortality will be assessed by comparing Kaplan-Meier curves via log-rank test. The number of serious adverse events will be compared via 2×2 tables with chi-square tests, or Fisher’s exact test in case the expected number under the null hypothesis is smaller than 1 in at least one of the cells. Number of AEs per individual will be compared using Poisson regression, or quasi-Poisson regression in case of overdispersion. EQ visual analogue score will be compared via linear regression in case it has a fairly symmetric distribution; otherwise we will use beta-regression. Normalization of neutrophils will be defined as first time to reach normal range of >2.0 ×10
^9^/l and for platelets the first time to reach >150 ×10
^9^/l and will be assessed by Cox model. For viraemia AUC and duration outcomes we will also perform the analysis with correction for day of illness (DOI). The time of fever clearance is defined by the first time after which all readings are <37.5°C in the following 48 hours.

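### The primary slope model, as described, includes neither ward-by-time nor explicit conditioning on baseline mSOFA; both are free to add and may recover some power

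*Protocol article*

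**What the plan says.** Under Randomization, the protocol article states: "Randomization will be minimization at 1:1 ratio and stratified according to the ward of recruitment". The Design section gives the two levels, intensive care or emergency department against the general dengue wards. No other allocation factor is named.

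The Primary endpoint section defines the outcome as a change from randomisation: "The primary endpoint of this study is the delta mSOFA score* (change in mSOFA score over 4 days after randomization". Under Statistical considerations, the Statistical analysis paragraph describes a linear mixed-effects model for the mSOFA values over the first 4 days, with a linear time trend as both a fixed and a random effect. Of the difference in slope between arms it says: "This difference will be assessed via the interaction between time and treatment group in that model".

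That paragraph does not mention ward in any analysis. It does not say whether the value at randomisation is the first response in the model, or whether the arms share a baseline mean. The one covariate it names is day of illness, for the viraemia outcomes.

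**The concern.** Balancing the arms on ward removes ward from the treatment contrast. If ward also predicts how fast mSOFA changes, a model without it still counts the between-ward variation in its standard error. The confidence interval is then wider than it need be and the test rejects less often than its nominal 5%. A split between intensive care or emergency patients and general-ward patients is a plausible predictor of 4-day change, although the article gives no data on this.

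Baseline mSOFA is a separate matter. If patients who start high tend to fall faster, a slope comparison that does not use the baseline leaves explainable variation in the error. That costs precision but does not disturb the type I error.

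The stake is power. The stated design inputs already give less than the intended 80%, so precision that can be had without more patients is worth taking.

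**Working it through.** **Inputs from Statistical considerations.** SD of the 4-day change 2.4, difference 1.0 point, 80 per group, 5% type I error. Sidedness is not stated; two-sided is taken from the 95% confidence interval. All powers use the normal approximation unless noted.

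**1. The plan's own figure.** n per group = 2 × (1.960 + 0.842)² × 2.4² / 1.0² = 90.4, so 91 rather than 80. At 80 per group the standard error is 2.4 × √(2/80) = 0.379, and power is Φ(1/0.379 − 1.960) = Φ(0.675) = 75.0% (74.5% with the t distribution). To reach 80% at 80 per group the SD would have to be √40 / 2.802 = 2.257. That means covariates explaining 1 − (2.257/2.4)² = 11.5% of the variance.

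**2. Leaving out ward when it predicts change.** Assume a 50:50 ward mix and a difference D between wards in mean 4-day change. D is not in the article. Keep the total SD at 2.4.

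- Within-ward SD: s = √(2.4² − 0.25 D²)
- True standard error with balanced wards: s × √(2/80)
- Type I error without ward: 2 × [1 − Φ(1.960 × 2.4 / s)]
- Power without ward: Φ[(1 − 1.960 × 0.379) / (s√(2/80))]
- Power with ward: Φ[1 / (s√(2/80)) − 1.960]

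| D | s | Type I error without ward | Power without ward | Power with ward |
|---|---|---|---|---|
| 0 | 2.40 | 5.0% | 75.0% | 75.0% |
| 1 | 2.35 | 4.5% | 75.5% | 76.9% |
| 2 | 2.18 | 3.1% | 77.1% | 82.6% |

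With the t distribution the powers with ward are 76.4% and 82.2%.

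**3. Check on slopes.** A simulation of per-patient slopes (20,000 runs) assumed days 0 to 4, 80 per arm, 40% in intensive care or emergency, slope SD 0.45 per day and residual SD 1.0. A ward effect on level alone (3 points) left type I error at 5.0% and power unchanged at 81.6%. Adding a ward effect on slope of −0.3 or −0.6 per day gave type I errors of 4.1% and 2.7% without ward. Power was 79.5% and 73.5% without ward, against 81.4% and 82.0% with ward-by-time. Here the within-ward variance is fixed, so power without ward falls as the ward effect grows. In step 2 the total SD is fixed, so it rises slightly. The direction of the comparison is the same.

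**4. Ward main effect alone.** In a random intercept-and-slope model, adding only a ward main effect leaves the standard error of time-by-treatment unchanged (ratio 1.000). It moves the intercept, not the slope.

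**5. Conditioning on baseline.** Assume intercept SD 2.4, slope SD 0.5 per day, residual SD 1.0, days 0 to 4 and intercept-slope correlation r. A patient's least-squares intercept and slope have covariance matrix C = G + (Z′Z)⁻¹, where (Z′Z)⁻¹ has entries 0.6, −0.2 and 0.1. So C₁₁ = 5.76 + 0.6 = 6.36, C₂₂ = 0.25 + 0.1 = 0.35 and C₁₂ = 1.2r − 0.2. Compared with a separate baseline level in each arm, a common baseline mean cuts the variance of the slope difference by C₁₂² / (C₁₁C₂₂), with C₁₁C₂₂ = 2.226:

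- r = 0: 0.04 / 2.226 = 2%
- r = −0.3: 0.3136 / 2.226 = 14%
- r = −0.5: 0.64 / 2.226 = 29%
- r = −0.7: 1.0816 / 2.226 = 49%

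**The case against.** The strongest objection is that this is a condensed article. Its analysis paragraph refers to numbered sections of a fuller document, and an analysis plan that is not shown may list covariates. Nothing in the text calls the model unadjusted. Naming day of illness for viraemia shows that some covariates are mentioned, not that the list is complete. This stands as a limit on confidence: the point applies to the model as published. It does not remove the point, because that model is specified down to its time terms and its test.

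Four stronger readings are tempting, and the article does not support them.

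- A reader might infer that leaving out either variable makes the test conservative. Only ward can, because it was used in allocation, and only if it predicts the slope. No section says that it does.
- A reader might infer that each arm has its own free baseline level. The text names no such term and is equally compatible with a common baseline mean, in which case the baseline gain is already taken. Nor is baseline necessarily unused: if the value at randomisation is a response, the slope already measures change from it.
- A reader might apply the familiar ratio of covariance analysis to change score, (1 + ρ)/2, and conclude that power rises to 86.1%, 83.8% or 81.5% for ρ of 0.5, 0.6 or 0.7. That ratio is for two time points with equal variances, not the planned slope model. Even on its own terms it gives only 79.3% at ρ = 0.8. If the SD grew from 2 to 3 with ρ = 0.6, the ratio would be 9 × 0.64 / (4 + 9 − 7.2) = 0.993, almost no gain.
- A reader might infer that the secondary analyses are invalid without ward. With ward balanced, the log-rank and Cox tests remain valid under the null, and no loss has been quantified for them.

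It is also fair that a 2-point ward difference is twice the target treatment effect. At 1 point the gain in power is little more than one percentage point.

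**Conclusion.** The point holds conditionally. As described, the primary slope model includes neither ward nor explicit conditioning on baseline mSOFA. If ward predicts the 4-day slope, omitting it makes the test mildly to moderately conservative (about 4.5% to 3.1% for assumed differences of 1 to 2 points). It forgoes between about one and five and a half percentage points of power. If ward shifts only the level, there is no cost. Not conditioning on baseline affects precision alone. The 2% to 49% range rests on assumed variances and on r between 0 and −0.7; in that model the gain vanishes at r near +0.17, where 1.2r − 0.2 = 0.

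There is no bias and no inflated error here. It is a worthwhile improvement rather than a flaw in validity. It matters mainly because the stated inputs give about 75% power. Covariates explaining about 11.5% of the variance would bring 80 per group to 80%, but nothing in the article shows whether ward and baseline explain that much.

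**What to change.** - In the primary mixed model, pre-specify ward and ward-by-time. A ward main effect alone is not enough.
- State that the value at randomisation is a response with a baseline mean common to both arms (constrained longitudinal model). Alternatively, model the post-baseline values with baseline mSOFA and baseline-by-time as covariates.
- Stratify the log-rank test by ward, and stratify or adjust the Cox models by ward. Add ward and ward-by-time to the laboratory slope models.
- If the full analysis plan already does this, align the published description with it.

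The cost is wording only. Ward is recorded for allocation, and the endpoint itself requires mSOFA at randomisation. The change should be fixed before unblinding, since covariates chosen afterwards are open to challenge. It should not be presented as a substitute for resolving the sample-size calculation.

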### Secondary endpoints

The secondary endpoints are: 30-day mortality; change in mSOFA score at day 7 post randomization; number of days in ICU; number of days in hospital; number of individuals with serious adverse events (time-period 1–5 days and 6–30 days); number of adverse events per individual during the whole study course; change in ALT and platelets over 5 days following randomization; change in ferritin and CRP levels over 5 days following randomization and until day 30 after illness onset; time to normalization of platelets (defined as >150 ×10
^9^/l) and neutrophils (>2 ×10
^9^/l); platelet nadir; fever clearance time (defined as <37.5 °C for at least 48 hours; measured 4 times/day); duration of viraemia (number of days to first negative qPCR and NS1); AUC viraemia (from enrolment to negative); EQ-5D-5L questionnaire score at hospital discharge and day 30.

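### The tests for 30-day mortality and serious adverse events leave out ward, the randomisation stratum: if ward is prognostic they stay valid but lose some power

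*Protocol article*

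**What the plan says.** The Randomization section states: "Randomization will be minimization at 1:1 ratio and stratified according to the ward of recruitment". The Design section defines two strata, ICU/Emergency Department and general dengue wards, and sets the size: "The study will enrol 160 adults and children ≥ 12 years old".

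The Secondary endpoints section opens with mortality: "The secondary endpoints are: 30-day mortality". It also lists the number of individuals with an SAE, in two windows (days 1–5 and days 6–30).

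The Statistical considerations section gives the tests. For mortality: "Mortality will be assessed by comparing Kaplan-Meier curves via log-rank test". For SAEs: "The number of serious adverse events will be compared via 2×2 tables with chi-square tests", with Fisher's exact test if an expected cell count is below 1. Ward is not mentioned for either, nor for any other analysis in that section. The section does name a correction for day of illness in the viraemia analyses.

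**The concern.** Balancing the arms within ward removes chance differences between the arms in ward mix. A test that ignores ward still counts the between-ward variation in its variance. If ward predicts the outcome, that variance is too large, the p-value is too large on average, and a real difference is missed more often.

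Ward probably is prognostic. Eligibility runs from a single warning sign to severe dengue, and the factor separates patients in intensive or emergency care from the rest. The Discussion links higher ferritin both to need for intensive care and to mortality, so the article treats these as related signs of severity.

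The cost is not only a missed benefit. For SAEs and excess deaths under an immunomodulator, a conservative test is also slower to show harm.

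**Working it through.** **Inputs from the article.** 160 patients, 1:1, stratified by ward in two strata. The article gives no power, expected deaths, ward-specific mortality or ICU/ED share for mortality, so there is no mortality figure to reproduce. Its only computed figure is 80 per group for delta mSOFA. With the stated SD of 2.4, difference of 1.0, 80% power and a two-sided 5% level, 2 × 2.4² × (1.960 + 0.842)² / 1.0² ≈ 90.4, that is 91 per group. That is a separate matter and does not bear on this point; 160 is taken as planned.

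**Assumed.** ICU/ED share 20–50%; 30-day mortality 5–40% in ICU/ED and 0.5–10% on general wards; hazard ratio 0.5 for power; two-sided 5%.

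**Step 1, approximate formula.** Let s be the ICU/ED share, p₁ and p₀ the 30-day risks in ICU/ED and on general wards, and p = s·p₁ + (1−s)·p₀. The plain test uses a variance proportional to p(1−p). With balance within ward, the variance of the contrast is proportional to s·p₁(1−p₁) + (1−s)·p₀(1−p₀). With r the ratio of the second to the first, the true size is about 2[1 − Φ(1.96/√r)].

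Example, s = 0.3, p₁ = 0.30, p₀ = 0.01:
- p = 0.090 + 0.007 = 0.097
- within-ward variance = 0.3 × 0.21 + 0.7 × 0.0099 = 0.0699
- total variance = 0.097 × 0.903 = 0.0876
- r = 0.798, and 1.96/√0.798 = 2.19
- size ≈ 2.8%

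**Step 2, simulation of the log-rank test.** Exponential death times censored at day 30, permuted blocks of 4 within ward (standing in for minimization by ward), 12,000 trials per scenario. Each pair is plain / ward-stratified.

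| ICU/ED share | Mortality ICU/ED, general | Mean deaths, no effect | Size by formula (plain) | Simulated size | Power at HR 0.5 |
|---|---|---|---|---|---|
| 30% | 10%, 10% | 15.9 | 5.0% | 5.2 / 5.2% | 20.5 / 20.5% |
| 30% | 5%, 0.5% | 2.9 | 4.7% | 2.7 / 2.8% | 2.7 / 2.7% |
| 30% | 10%, 1% | 5.9 | 4.5% | 4.1 / 4.8% | 8.7 / 9.5% |
| 50% | 10%, 1% | 8.8 | 4.6% | 4.5 / 5.1% | 11.8 / 13.3% |
| 30% | 20%, 1% | 10.7 | 3.7% | 3.4 / 4.6% | 12.7 / 15.8% |
| 50% | 20%, 1% | 16.8 | 3.9% | 3.4 / 4.3% | 19.7 / 21.9% |
| 30% | 30%, 1% | 15.5 | 2.8% | 2.7 / 4.7% | 15.8 / 20.7% |
| 50% | 30%, 2% | 25.5 | 3.4% | 3.6 / 5.2% | 28.1 / 32.2% |
| 20% | 40%, 1% (extreme) | 14.1 | 1.9% | 1.9 / 5.2% | 13.0 / 20.2% |

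A separate simulation (exact balance within ward, 8,000 trials per scenario, 60% relative reduction) gave plain sizes of 2.6–4.2% and power gains of 2.2 to 6.7 points. In the shared scenario of 30% versus 1% with 30% in ICU/ED, its sizes were 2.6 / 4.7%. The two sets differ by up to about 0.8 points in absolute size (for example 4.1% and 3.4% at 20% versus 1%, half each). Simulation error is about 0.2 points per estimate, √(0.05 × 0.95/12,000), and the balancing devices differ.

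**Step 3, SAEs.** Assumed SAE risks, 80 per arm balanced within ward, 200,000 runs, risk ratio 0.5 for power. Each pair is plain chi-square / Cochran-Mantel-Haenszel.

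| SAE risk ICU/ED, general | ICU/ED share | Size | Power |
|---|---|---|---|
| 30%, 10% | 50% | 4.4 / 5.1% | 42 / 44% |
| 40%, 10% | 50% | 3.9 / 4.9% | 53 / 57% |
| 50%, 10% | 30% | 2.9 / 4.9% | 46 / 53% |
| 20%, 20% | any | 5.0 / 5.0% | 42 / 43% |

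**Step 4, what limits mortality.** For HR 0.5 with 80% power, Schoenfeld's formula needs 4 × (1.960 + 0.842)² / (ln 0.5)² ≈ 65.3, that is 66 deaths. The simulated trials at HR 0.5 had about 2 to 20. Power is then about 3% to 32% with either test.

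**The case against.** The strongest objection is that this rests on silence in a condensed article. The text says log-rank without saying unstratified. It refers to sections 2.4.1 and 2.4.2, which the article does not contain, so it was taken from a fuller document. No analysis in it mentions ward, including the primary mixed model. The full protocol or SAP may stratify.

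That lowers the priority but does not remove the point. The section names each test, sets a rule for switching to Fisher's test, and states a covariate correction where one is wanted. A single 2×2 table cannot carry ward. As written, these are plain tests; if the SAP differs, the two texts need aligning.

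Four stronger readings are tempting and not supported:
- A reader might infer that the mortality test is definitely too conservative. That depends on ward-specific rates the article does not give. With equal rates there is no difference. With about three deaths both tests fall well below 5% because events are sparse, and stratifying gains nothing.
- A reader might infer that the tests are invalid. They are not; the type I error is not inflated.
- A reader might blame the low power for mortality on the missing stratification. It comes mainly from few deaths.
- A reader might take mortality to be the outcome with the fewest events. That is plausible, but the article does not say so.

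It is also fair that the gain is small and that these are secondary endpoints of a phase II trial sized on delta mSOFA.

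**Conclusion.** The point holds in conditional form. The stated tests for 30-day mortality and SAEs do not use the factor on which allocation is balanced. Where ward is assumed prognostic and deaths are not very few, true size is about 2.6% to 4.5% (1.9% in the extreme case) and the power loss is about 1 to 7 points. These figures rest on assumed rates and ICU/ED shares, and on blocks or exact balance within ward standing in for minimization. Stratifying cost no power in any scenario examined. It has more practical value for SAEs, where events may be more numerous, than for mortality, where it leaves power low. This is a free improvement on secondary endpoints, of low priority.

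**What to change.** In the analysis text, before unblinding:
- stratify the log-rank test for 30-day mortality by ward of recruitment (ICU/ED versus general);
- compare individuals with an SAE in each of the two windows by a Cochran-Mantel-Haenszel test stratified by ward, with an exact stratified version where cells are sparse, in place of the present Fisher fallback;
- keep the plain log-rank and 2×2 tests as a check.

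If the SAP already does this, only the published wording needs aligning. The cost is a few words: ward is already held in the randomisation system, and no new data or patients are needed. A general-ward stratum with very few deaths will add little information to the mortality test.

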### Inclusion and exclusion criteria

Patients will be eligible for study enrolment if they: (i) are more than or equal to 12 years of age; (ii) have a clinical diagnosis of dengue and at least one warning sign or severe dengue (based on the World Health Organization (WHO) 2009 or Vietnamese Ministry Of Health (MOH) – Dengue guidelines)
^
23,
24
^; (iii) have plasma ferritin levels > 2000 ng/mL ; (iv) agree to come back for two follow up visits between day 30 – 35 and at around day 90 afterillness onset; and (v) provide written informed consent.

Exclusion criteria include: (i) pregnancy (confirmed by either clinical examination or urine dipstick for human chorionic gonadotropin hormone); (ii) localizing features suggestive of an alternative diagnosis; (iii) taking immunosuppressive drugs or other biologics in the last month; (iv) underlying malignancy or immunosuppression; (v) children less than 12 years of age; (vi) have baseline GFR < 30 ml/min; (vii) having a neutrophil count < 1.0 × 10
^9^/L; (viii) being treated for tuberculosis; (ix) HBsAg-positive; (x) taking any drug with significant interaction with anakinra (concomitant medication and drug interactions); (xi) patients who are considered unlikely to attend follow-up visits because of long travelling distance to the study clinic or other reasons.

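### Platelet and neutrophil normalization is scored at the first value above the threshold, with no below-threshold start and no persistence condition, so entry, pre-nadir and transient values can count as recovery

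*Protocol article*

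**What the plan says.** Under Statistical considerations, the protocol article states: "Normalization of neutrophils will be defined as first time to reach normal range of >2.0" ×10⁹/L, "and for platelets the first time to reach >150" ×10⁹/L, "and will be assessed by Cox model". The Secondary endpoints section lists the same two thresholds and adds no condition on the starting value or on how long the value must hold.

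At entry, the only neutrophil limit is an exclusion for "having a neutrophil count < 1.0" ×10⁹/L. There is no platelet limit. The one laboratory threshold among the inclusion criteria is "have plasma ferritin levels > 2000 ng/mL".

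The same statistical paragraph treats temperature differently: "The time of fever clearance is defined by the first time after which all readings are <37.5°C in the following 48 hours".

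**The concern.** A time-to-recovery endpoint presupposes that the patient is abnormal when the clock starts and stays recovered once the event is declared. The stated rule secures neither. Three kinds of value can satisfy it without being recovery:

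- a count already above the threshold at randomisation;
- a count above the threshold while still falling towards the nadir;
- a single transient high reading.

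An event settled before the first dose cannot reflect treatment, and one triggered by a pre-nadir or isolated value reflects it poorly. If such events are kept in the Cox model, they pull the hazard ratio towards 1. If the software or the analyst drops the time-zero ones, the analysis set shrinks in a way the document does not state. In either case the reported hazard ratio is hard to interpret as a treatment effect on recovery.

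**Working it through.** The plan gives no event count, power or sample size for this endpoint, so there is no stated figure to reproduce. The check sets the text side by side and then illustrates scale.

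**Text**

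| Question | What the protocol article says |
|---|---|
| Can patients enter above 2.0 neutrophils? | Yes; only counts below 1.0 are excluded |
| Can patients enter above 150 platelets? | Yes; no limit is set |
| Are falls after entry anticipated? | Yes; platelet nadir is a secondary endpoint, and Safety review and monitoring has a drug-stopping criterion at neutrophils below 0.5, under the entry limit of 1.0 |
| Must the count be low at the start? | Not stated |
| Must the value persist? | No for counts; 48 hours for fever clearance |

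**Power if events at entry carry no information**

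Inputs: 160 patients (from the document). Assumed: hazard ratio 1.5, every patient eventually normalises, two-sided 5%. The share above threshold at entry is not given, so it is varied. With 1:1 allocation and D informative events, z = √D × ln(1.5)/2 − 1.96, where ln(1.5)/2 = 0.2027, and power = Φ(z).

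| Above threshold at entry | Events at time zero | D | z | Power |
|---|---|---|---|---|
| 0% | 0 | 160 | 2.564 − 1.96 = 0.604 | 73% |
| 10% | 16 | 144 | 2.433 − 1.96 = 0.473 | 68% |
| 25% | 40 | 120 | 2.221 − 1.96 = 0.261 | 60% |
| 50% | 80 | 80 | 1.813 − 1.96 = −0.147 | 44% |

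**Dilution if the early events stay in the model**

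This is a simulation of 200 runs with 80 patients per arm and daily V-shaped neutrophil counts. All trajectory inputs are assumed: median entry count 1.5, 2.0, 2.5 or 3.0; mean log fall 0.5 to a nadir on day 1–3; an extra log fall of 0.3 in one arm. A hazard ratio below 1 means slower normalisation in that arm. Time-zero events were kept in the fit.

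| Above 2.0 at entry | Of these, later at or below 2.0 | HR, first value | HR, first sustained value | Power, first value | Power, sustained |
|---|---|---|---|---|---|
| 26% | 87% | 0.70 | 0.63 | 57% | 79% |
| 50% | 79% | 0.79 | 0.64 | 30% | 77% |
| 69% | 70% | 0.86 | 0.63 | 14% | 82% |
| 82% | 62% | 0.92 | 0.64 | 6% | 81% |

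The simulated sustained rule was applied to all patients and required every later reading to stay above 2.0. It therefore shows the direction of the effect; it does not measure the fix proposed below.

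**The case against.** The strongest reply has four parts.

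*Falls are captured elsewhere.* A reader might infer that the rule makes later falls invisible or hides a neutropenia signal. The documents do not support that. Platelet nadir and the 5-day platelet change are separate secondary endpoints, the latter with its own mixed model. Adverse events are all recorded, clinical and laboratory events are graded by CTCAE, severe neutropenia is a stopping criterion, and the DMC reviews safety after 10 patients and then after every 50. This objection stands. What remains is narrower: no neutrophil nadir or neutrophil change endpoint is listed.

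*Time-zero scoring is inferred.* The article does not say how patients already above the threshold are handled. The wording could be read as presupposing an abnormal start, and an unseen analysis plan could restrict the risk set. This stands in part. Restricting the risk set would not supply the missing persistence condition, because the first-value definition is fixed in the text.

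*Bias or power, not both.* If time-zero events drop out of the fit, a pre-randomisation subset is left, and those patients cost power without biasing the comparison. Attenuation needs those events to be kept, or crossings after entry but before the nadir. This is correct, and the document does not settle which case applies.

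*The size is unknown.* One might put the share above 2.0 at entry at 20–40%, which would be 0.20 × 160 = 32 to 0.40 × 160 = 64 patients, but nothing in the document supports that range. This stands.

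A first-crossing time is also simple and reproducible. But the plan itself saw the need for persistence in its definition of fever clearance.

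**Conclusion.** The point holds as a weakness in how a secondary endpoint is defined; the primary endpoint is untouched. The stated rule allows entry, pre-nadir and transient values to count as normalization, in a population that may enter above either threshold and in which the plan itself anticipates falls.

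The direction follows from the definition: loss of power, or dilution towards no difference. The size cannot be derived from the documents. Under the assumed hazard ratio of 1.5 the power loss is modest when 10–25% are above threshold at entry (73% to 68–60%) and large at 50% (44%), on an endpoint for which the trial was not sized. The simulated dilution depends entirely on assumed trajectories.

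The weakness matters most for neutrophils, because platelets have two other endpoints that register a fall. It does not show that a safety signal would be missed.

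**What to change.** Amend the definition and analysis, before unblinding, as follows:

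1. Analyse time to normalization in patients at or below the relevant threshold at randomisation. This subset is fixed before randomisation, so the comparison between arms stays fair. State how many patients are outside it, by arm.
2. Define the event as the first value above the threshold that persists in the following readings, in line with the 48-hour condition for fever clearance. State a rule for a first high value on the day of discharge, when daily readings end and the next scheduled count is at the day-30 visit.
3. Treat death as a competing event: a patient who dies without the event never normalised.
4. Report the lowest post-dose neutrophil count by arm in all randomised patients, so that patients who start above 2.0 and then fall are seen.

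Applying a sustained-value rule to all randomised patients would not be enough. Anyone above the threshold throughout would still have the event at time zero, hence item 1.

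The cost is wording and programming; the Data collection section already provides a full blood count at each daily review until discharge. The statistical price is fewer patients in the time-to-event analysis and slightly later event times. Item 1 does not win back the power lost to patients above threshold at entry; it makes the comparison explicit and removes their dilution.
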